## Abstract

Diabetic foot ulcer (DFU) is the leading cause of lower-limb amputations, with a significant impact on patients, families, and society. Since DFU medical treatments represent a major socioeconomic burden, cost-effective interventions are needed. This trial aims to assess the effectiveness of a muscle relaxation intervention compared to a hypnosis intervention versus active and passive control groups on DFU healing, physiological indicators of healing prognosis, and quality of life (QoL) in clinically distressed patients with a chronic DFU. A multicenter, randomized controlled trial with three assessment moments (baseline, two months post-intervention, and four months follow-up) will be conducted. Approximately 170 patients will be randomized and allocated to either treatment or control groups. Primary outcomes will be DFU healing, physiological indicators of healing prognosis, and QoL. Secondary outcomes will include perceived stress, psychological morbidity, and DFU representations. The efficacy of sessions on DFU healing will be qualitatively assessed in 12 patients allocated to the treatment and active control groups, as well as their family caregivers. This study will provide evidence regarding the effectiveness of two psychological interventions for the DFU healing process and the QoL of patients, with direct clinical relevance regarding DFU treatment and recurrence.

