## 1. Background

Diabetes represents a growing public health concern with a growing global incidence during the last three decades [1] due to lifestyle changes and aging. According to the International Diabetics Federation, in 2021, an estimated 6.7 million adults have died as a result of diabetes or its complications. Over time, patients with diabetes have an increased risk of developing serious comorbidities, such as cardiovascular disease, blindness, kidney failure, and foot ulcerations [2].

Diabetic foot disease is one of the most serious complications of diabetes, impacting nearly 15% of all patients [3]. Diabetic foot ulcer (DFU) is a full-thickness wound below the ankle, in most cases, caused by poor glycemic control, calluses, ill-fitting footwear, underlying neuropathy, peripheral vascular disease, or improper foot care. Around 11–14% of worldwide patients diagnosed with diabetes will develop DFUs [4], which is the leading cause of lower-limb amputations in approximately 80% of these patients [5]. According to Zhang et al., the current DFU prevalence worldwide was 6.7%, while in Europe was 5.1% [6].

In addition to the devastating consequences of DFU development to patients and their families, the socioeconomic cost involved has become a burden. From 2007 to 2021, the direct cost of DFU treatment worldwide has increased from USD 232 to 966 billion, which reflects a dramatic increase. In Europe alone, the total medical costs for the management of DFUs in 2010 were estimated to be USD 105.5 billion, while in 2030, it is expected to reach USD 124.6 billion [2]. Thus, planning cost-effective interventions focused on DFU recovery becomes essential. This is also true regarding the impact on the environment, fewer trips to DFU clinics, fewer hospitalizations, and less clinical waste produced.

It is known that adherence to self-care behaviors and treatment is essential to wound healing. However, psychological factors, such as depression or anxiety, may also negatively influence DFU healing via psycho immunological effects [7,8]. Furthermore, DFU is associated with distress [9], and negative emotions contribute to prolonged infections, delayed wound healing, and poor quality of life (QoL), which is associated with low treatment responses and low remission rates, a major health concern [7,10,11].

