#### 3.3.1. Degree of DFU Healing

Wound healing is defined as the complete epithelization of the wound and is assessed through the RESVECH 2.0-PT [41], a useful and validated tool to monitor the progression of chronic wounds of any etiology through six main parameters: wound area, depth and involved tissues, wound margins, type of tissue in the wound bed, levels of exudates, and presence of signs of infection/inflammations. This questionnaire will be filled out by the participant’s physician or nurse at the end of consultations to monitor DFU progression. Scores range from 0 to 35, where zero indicates complete healing and 35 corresponds to the worse possible wound.

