### 3.5. Other Outcome Measures

Health literacy, blood pressure, heart rate, time to complete wound healing, and time to favorable healing prognosis will also be assessed.

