#### 3.5.4. Time to Complete Wound Healing

This variable corresponds to the time interval (days) between the baseline assessment and the complete DFU healing.

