### 5.2. Data Analysis

The baseline data of the treatments and control groups will be compared using the chi-squared test for binary variables and the independent sample t-test for continuous variables. To prevent overestimating the impact of both interventions, an intention-to-treat approach will be assumed to evaluate the impact on the primary and secondary outcomes. The comparison between the treatment groups versus control groups over time (differences between and within) will be performed through mixed general linear models of analysis of variance for repeated measures. Effect sizes (Cohen’s d coefficient) will also be provided between T0 and T1, T1 and T2, and T0 and T2 to determine if the intervention shows any treatment effect. A significance level of 0.05 will be set for a two-sided test, and the 95% confidence interval will be calculated. In addition, time to complete wound healing and time to favorable healing prognosis (based on the wound size) will be estimated using survival analysis, specifically, single variable and multivariable Cox proportional hazard ratio regression models and Kaplan–Meier plots. All previous analyses will include the DFU stage at the baseline as a control variable. Other confounding clinical factors associated with the outcome variables will also be considered in the statistical analysis.

The data will be analyzed using the Rstudio, R version 3.6.2 (R Core Team, Vienna, Austria) and the SPSS statistics, v. 24.0 (IBM Corp., Armonk, New York, NY, USA).

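### If patients who die or lose the index ulcer by amputation are censored, the planned Kaplan-Meier plot of time to healing overstates the proportion healed; a cumulative incidence curve would not

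*Protocol article*

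**What the plan says.** Section 5.2 states that "time to complete wound healing and time to favorable healing prognosis (based on the wound size) will be estimated using survival analysis", and names the tools: "single variable and multivariable Cox proportional hazard ratio regression models and Kaplan–Meier plots". Section 3.5.4 defines the variable as "the time interval (days) between the baseline assessment and the complete DFU healing". Section 3.3.1 gives the meaning of healing: "Wound healing is defined as the complete epithelization of the wound".

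The article gives no rule for a patient who dies, or whose index ulcer is removed by amputation, before healing. It names neither a cumulative incidence curve nor a cause-specific or subdistribution analysis. Section 3.5 places time to healing among the other outcome measures: "Health literacy, blood pressure, heart rate, time to complete wound healing, and time to favorable healing prognosis will also be assessed".

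Amputation appears in the Abstract, the Background and the Discussion as part of the burden of the disease. It is not an endpoint, an exclusion criterion or a stated end of follow-up.

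**The concern.** Kaplan-Meier estimation assumes that a censored patient could still have the event later, at the same rate as patients who remain under observation. That is reasonable for someone who moves away. It does not fit someone who has died or whose ulcer site has been amputated, because that ulcer can no longer epithelialise.

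If these patients are censored, the curve describes healing in a hypothetical population without amputation or death. A reader will usually take it as the share of patients healed by a given day, and for that use it is too high. If amputation or death is more frequent in one arm, that arm's curve is raised more, which favours the arm that did worse on those events.

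**Working it through.** **Inputs**

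- Method: Kaplan-Meier and Cox (section 5.2).
- Event: complete epithelization of the index ulcer (section 3.3.1), timed from baseline (section 3.5.4).
- Patients per group: 42 (section 5.1).
- Healing probability, amputation rate and death rate: not given. The values below are assumptions. The article has no figure of its own to reproduce on this point.

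**Direction of the error**

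Let S(t) be the probability of being alive, unhealed and not amputated at the index site at time t. Let K(t) be the Kaplan-Meier curve with amputation and death censored. The true proportion healed accumulates S(t) × healing hazard, whereas one minus Kaplan-Meier accumulates K(t) × healing hazard. K(t) is never below S(t), so the error can only be upward. This does not require constant hazards.

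**Size of the error under constant hazards**

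Let H be the true proportion healed by the end of follow-up and C the proportion with amputation or death first.

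1. Total cumulative hazard = −ln(1 − H − C).
2. Healing part = total × H / (H + C).
3. One minus Kaplan-Meier = 1 − exp(−healing part).

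With H = 0.50:

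| C | Total hazard | Healing part | 1 − KM | Excess (points) |
|---|---|---|---|---|
| 2% | −ln 0.48 = 0.734 | 0.706 | 50.6% | 0.6 |
| 5% | −ln 0.45 = 0.799 | 0.726 | 51.6% | 1.6 |
| 10% | −ln 0.40 = 0.916 | 0.764 | 53.4% | 3.4 |
| 20% | −ln 0.30 = 1.204 | 0.860 | 57.7% | 7.7 |

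Over the same range of C, the excess runs from 0.5 to 5.7 points if 40% truly heal and from 0.8 to 10.1 points if 60% do.

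The length of follow-up cancels out. Section 2.2 gives six months in all, while section 3.1 implies about eight (T1 at two months, T2 six months later). These must be reconciled for the time axis of the plot, but the table is unaffected.

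**Check by simulation**

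In 400,000 simulated patients with H = 50% and C = 10%, one minus Kaplan-Meier was 53.5% against a true 50.1%. Keeping the amputated or deceased patients at risk as unhealed to the end of follow-up gave 50.1%, so the error disappears under that rule.

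**Comparison between arms**

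- Equal healing (50%) and equal C: both curves rise by the same amount and no gap appears.
- Equal healing (50%), C = 5% v 15%: 51.6% v 55.4%, a false gap of 3.8 points in favour of the arm with more such events.
- Unequal healing (40% v 60%), C = 10% in both: 42.6% v 64.4%. The true gap of 20 points reads as 21.8, a slight stretch of a real difference.

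**Sampling error for scale**

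With 42 patients per group and 50% healed, the standard error of one proportion is √(0.5 × 0.5 / 42) = 7.7 points. For a difference between two groups it is √2 × 7.7 = 10.9 points.

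**The case against.** The strongest reply is that the article never says these patients will be censored. Censoring rules usually belong in a statistical analysis plan, which is not shown, and if such patients stay at risk as unhealed there is no error. This stands in part: the overstatement is conditional and cannot be asserted outright. However, the article does choose the type of curve, and a better type is available at almost no cost. The point is therefore about a named method and not about missing detail.

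A second reply is that the events may be rare. The amputation statements, such as "which is the leading cause of lower-limb amputations in approximately 80% of these patients", describe disease burden and give no rate expected in this trial. Section 2.3 also excludes relapsed ulcers, three or more ulcers, hemodialysis, transplant and cancer. This stands: at 2% the excess is under 1 point, well inside sampling error. On the other side, section 2.4 stratifies by arterial and kidney disease as markers of poor prognosis, so such patients are enrolled and the events cannot be assumed absent.

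Three stronger readings are tempting, and the document supports none of them:

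- **The Cox analysis is wrong.** It is not. With these events censored it estimates the cause-specific hazard ratio of healing, which is valid but is not an effect on the probability of healing.
- **The arms will be badly distorted.** A 20% v 5% split in events would produce a false gap of 57.7 − 51.6 = 6.1 points. Nothing in the article suggests so large a contrast between arms that all receive standard ulcer care.
- **The trial's healing conclusion is at risk.** The primary healing outcome is the RESVECH 2.0 score, analysed by repeated-measures models, and does not depend on this curve.

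**Conclusion.** The point holds in conditional form. If patients who die or lose the index ulcer by amputation are censored, the Kaplan-Meier plot overstates the proportion healed. The direction is certain under that rule, but the size is not known. With 50% truly healed and constant hazards, both assumed, the excess runs from 0.6 points at 2% with such events to 7.7 points at 20%. A false difference between arms that heal equally requires the events to differ by arm. Only a descriptive plot of an outcome ranked below primary and secondary is affected. It is worth changing because the change is easy and the error does not shrink as the sample grows.

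**What to change.** In section 5.2, replace the Kaplan-Meier plot of time to complete healing with a cumulative incidence (Aalen-Johansen) curve for each arm, treating amputation at the index site and death as competing events. Describe the Cox result as a cause-specific hazard ratio for healing. A Fine-Gray analysis, in which such patients count as not healed to the end of follow-up, can be added but is optional.

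The cost is a few lines of code in R, which section 5.2 already plans to use, and one additional curve for the competing events. The dates of index-site amputation and of death must be recorded. The clinical questionnaire in section 3.2.2, completed by the physician or nurse at all three assessments, is a natural place for them. Sample size, visits and care are unchanged.

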## 6. Ethics

Only patients that provide written consent to participate in the trial and sign a consent form (to allow access to their medical records) will be included in the study. The consent process continues throughout the study as researchers review study procedures and confirm patient’s wish to continue at each session and assessment moment. All participants will be aware that they are free to withdraw from the trial at any time without any effect on their future standard of care medical treatment. For the qualitative nested study, patients and caregivers will receive a specific written informed consent to be signed.

The personal data of participants will be kept confidential before and during the study by pseudonymization, with the participant’s name being coded. Names and other identifying information will be kept on a single page in the database, only accessible to Researcher 1. At the end of the study, participant anonymization will be fully guaranteed. All personal data collected within the framework of this study will be preserved until the final publication of the results, not exceeding a five-year period. After this period, all data will be destroyed (paper records and biochemical samples) or eliminated (database records).

## 7. Discussions

Given the huge challenge of distress in patients with DFUs, and the limited data evaluating the healing process and QoL of patients with chronic DFUs, the study of the efficacy of two economic stress reduction interventions in clinically distressed patients with chronic DFUs is proposed.

This paper describes the PSY-DFU study protocol, the first national and international multicenter study to address the contribution of psychological variables in DFU healing and QoL. The study also tests the effects of two psychological interventions: individual relaxation and hypnosis, both with guided imagery, on wound healing, physiological indicators of wound healing prognosis, and QoL.

Many complicating factors of diabetes compromise the healing process, making effective treatments challenging. The compliance rate in the treatment groups is one of the major difficulties experienced so far. This is, in part, due to the fact that patients with chronic DFUs often present a long history of medical care, and yet many fail to adhere to the medical treatment and self-management, thus developing negative expectations about psychological interventions. Moreover, in the treatment groups, when DFU is completed healed, the intervention ends, which also contributes to the low-rate compliance. Regarding the DFU progress monitoring, this study would benefit from more advanced and accurate techniques to assess wounds, such as imaging devices. However, none of the three participating hospitals have yet adopted imaging systems to routinely measure DFUs. In addition to the limited strategies to improve adherence to treatments, and the use of more traditional tools to measure chronic DFUs, the non-fully blinded design also represents a limitation of this research.

The multicenter and randomized design of this PSY-DFU study, together with the used mixed-methods approach, is one of its major strengths. Results will answer the question, “Which psychological intervention is more effective and has more impact on the primary and secondary study outcomes in clinically stressed patients?” The findings will help to clarify the mechanistic underpinnings of the relationship between distress and chronic wound healing, the knowledge that is still very limited in general and nonexistent in DFU. The RCT is enhanced by the qualitative nested study, as qualitative data are expected to refine findings regarding the effectiveness of each intervention, allowing a better understanding of the impact of psychological factors on the DFU healing process.

Finding psychological and biological clues from specific patient groups with chronic DFUs will help health professionals tailor better treatments with precision that could prevent future diabetic foot wounds from developing or from recurring. Specifically, identifying the specific risk profile of patients will best provide health professionals with important information regarding their psychological vulnerabilities, which may make it difficult for DFU healing. Additionally, survival analysis will help to identify the best assessment moments to initiate psychological interventions to contribute to the DFU healing, and prevent the onset of new wounds. Therefore, this study is of important clinical relevance regarding DFU healing and recurrence, as well as QoL, and may also contribute to the decrease in health care and medical-related costs associated with DFU treatments, including amputations.

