#### Primary Specific Aims

The primary specific aims of this RCT are: (i) to compare the impact of both treatment groups (TG1 and TG2) in regard to DFU healing, physiological indicators of healing prognosis (biochemical parameters, inflammatory and angiogenic markers, miRNAs, and immune cells), and QoL, compared to control groups; (ii) to compare patients pre and post-intervention in the TG1 and TG2, controlling for patients’ health literacy, clinical characteristics (e.g., duration of diabetes and DFU, type of diabetic foot), and sociodemographic variables (e.g., gender, age, education, socioeconomic level); and (iii) to compare the efficacy of TG1 and TG2 versus ACG to DFU healing, according to participants and their respective family caregiver’s perceptions.

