### 2.3. Participant Recruitment and Selection Criteria

Patients with chronic DFU attending the first consultation of the multidisciplinary outpatient clinical of diabetic foot ulcer from three major hospitals in Northern Portugal will be recruited. In the first consultation, researchers (Researchers 1, 2, and 3) will collect the clinical information of each patient to signalize those that meet eligibility criteria. Patients will be consecutively enrolled in the study.

The inclusion criteria are: (i) being 18 years old or more, (ii) having one or two diabetic chronic ulcers (a non-healing ulcer for six or more weeks and less than 12 weeks; in case of patients with two active chronic DFUs, the ulcer with the largest area will be selected as the index ulcer) at the time of baseline assessment, (iii) reporting clinical levels of psychological distress, and iv) providing written informed consent. Clinical distress is assessed according to the Hospital Anxiety and Depression Scale (HADS) [33] and the Perceived Stress Scale (PSS) [34], with patients scoring ≥11 on the HADS subscales or ≥13 (male patients) and ≥17 (female patients) on the PSS evaluated as being clinically distressed.

Exclusion criteria include: (i) the DFU, at the time of baseline assessment, being a relapse; (ii) having three or more DFUs at the time of baseline assessment; (iii) having undergone a transplant; (iv) being on hemodialysis treatment; (v) having a cancer disease; (vi) having degenerative dementia or severe psychiatric illness (e.g., schizophrenia), (vii) receiving psychological counseling, or (viii) taking psychiatric medication during the study period.

For the qualitative study, participants that completed at least 75% of the intervention sessions or placebo sessions (active control group) will be invited to participate, together with their family caregiver. Participants will be purposively selected according to the type of diabetic foot (neuropathic versus neuroischemic) and DFU progression (positive versus negative). The sample will also be selected according to participants’ capacity to provide in-depth and rich-textures information regarding the intervention’s effectiveness since qualitative purposive sampling is considered to be more efficient than random sampling [35]. Thus, the quantitative study sample will include four single-per-participant interviews per group (4 conditions × 3 groups), in a total of 12 patients’ interviews and 12 caregivers’ interviews.

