## 3. Outcomes and Measures

### 3.1. Participant Timeline

Participants in the intervention and control groups will be assessed at the pre-intervention baseline (T0), at the end of the intervention/two months later at post-test (T1), and six months after T1 at the follow-up (T2). Data will be collected through face-to-face interviews conducted by health psychologists (Researchers 1, 2, and 3). Regarding the biochemical sample collection (biochemical parameter, inflammatory and angiogenic markers, miRNAs, and immune cells), a blood sample will be collected during the consultation at the T0, T1, and T2 assessment moments (Table 1).

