#### 4.1.1. Intervention Groups

Participants in the intervention groups are allocated in TG1 or TG2. Participants allocated to TG1 will receive four individual sessions of muscle relaxation with guided imagery (MR + GI), a technique of alternately tensing and relaxing muscle groups individually throughout the body. Relaxation intervention begins with diaphragmatic breathing, followed by Jacobson’s progressive muscle relaxation, which involves the contraction and subsequent relaxation of the 16 muscle groups of the body (hand, forearm, biceps, upper forehead, eye, nose, mouth, jaw and throat, neck, shoulder, chest, stomach, thigh, leg, and foot). The contraction will be performed for seven seconds while the relaxation lasts for about 40–50 s. The relaxation of the foot muscle group will not be performed on the foot with the wound because dressing and bandages may restrict the foot movements and, together with the typical joint stiffness of the diabetic foot, will render difficult the performance of exercise. After the muscle relaxation exercises, the guided imagery focused on the DFU healing process will initiate. The participant will be instructed to think about his/her current state of health and to imagine the DFU as a decreasing dark area and the healing process as a light associated with pleasant sensations. After being trained by the Lead Researcher, Researcher 1, 2, or 3 will be responsible for conducting the TG1 sessions in the respective hospitals.

In the TG2, participants will benefit from four individual sessions of hypnosis with guided imagery (H + GI), conducted by three qualified hypnotherapists external to the research study. The first session begins with the Eye-Roll Test for Hypnotizability [48]. Each session follows the Hypnotic Protocol with the following steps: pre-talk/absorption/ratification/alitiation/dissociation/awakening. All hypnotic sessions will train participants in the visual, auditory, and kinesthetic perception of ulcer healing, and will also promote medical treatment adherence.

The protocol for both treatment groups includes four scripted sessions, each one with duration of approximately 45 min, delivered once every two weeks, resulting in approximately a 2-month treatment course. Sessions will be conducted in a consulting room reserved by the hospital for the study, where patients will lie on a specialist couch.

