#### 4.1.2. Control Groups

Participants in the ACG will receive neutral guided imagery sessions, i.e., sessions focused on the patient’s daily life before the DFU. Neutral sessions are conducted by Researchers 1, 2, and 3 following a scripted protocol that includes four biweekly sessions of approximately 45 min, each one dedicated to a different topic (family, work, friends, and leisure). Initially, the participant will be asked to choose a specific event related to the topic of the session, positive or negative, without telling the researcher which event he/she thought about. Then, the participant will answer several questions regarding the episode to promote a more detailed reconstruction of the event, being instructed to only think about the answers and not to reply orally. When the whole episode is remembered, the participant will be asked to tell what he/she imagined/remembered regarding each of the questions. The goal of the placebo sessions is to control for the effect of the received attention, from psychologists and hypnotherapists, on patients in the treatment groups. It is possible that the privileged contact may positively influence the patient’s healing process. Therefore, the attention control condition will allow us to differentiate between the impact of interventions versus the attention given to the ACG.

Participants in the PCG will not receive any intervention besides the standard of care medical/nurse treatment. Both passive and active control patients will complete the same outcome questionnaires as the participants allocated to the interventions, at the same time intervals.

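### The Discussion ends treatment-group sessions at healing, a stop that the intervention sections do not contain; with the 75% session rule it makes interview eligibility depend on healing, and read literally it leaves attention unmatched

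*Protocol article*

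**What the plan says.** **Planned sessions.** Section 4.1.1: "The protocol for both treatment groups includes four scripted sessions, each one with duration of approximately 45 min, delivered once every two weeks", making a course of about two months. Section 4.1.2 describes the ACG sessions as "following a scripted protocol that includes four biweekly sessions of approximately 45 min" and gives their purpose as controlling for the attention that treated patients receive. For the fourth arm: "Participants in the PCG will not receive any intervention besides the standard of care medical/nurse treatment". None of these descriptions mentions healing as a reason to end sessions.

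**Stop at healing.** Section 7, while discussing difficulties met so far with compliance, adds: "in the treatment groups, when DFU is completed healed, the intervention ends, which also contributes to the low-rate compliance". The Primary Specific Aims show which arms the term covers: "to compare the impact of both treatment groups (TG1 and TG2) in regard to DFU healing".

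**Interview eligibility.** Section 2.3: "participants that completed at least 75% of the intervention sessions or placebo sessions (active control group) will be invited to participate". The same paragraph selects interviewees by type of diabetic foot and by positive or negative ulcer progression, four per group in TG1, TG2 and ACG. The interviews serve primary aim (iii), the perceived efficacy of TG1 and TG2 against ACG for healing.

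**The concern.** The article states two session rules for the treatment arms. One is a fixed course of four. The other, reported as practice, is four or fewer depending on when the ulcer heals. For ACG it states only the fixed course.

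Two things are at stake.

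1. **Interview sample.** A session threshold combined with a stop at healing turns an adherence criterion into selection on the outcome. The earliest healers are clear cases of positive progression, and the two rules together remove them from a sample that is meant to span progression.
2. **Attention control.** If ACG sessions run on after healing while treatment sessions do not, healed patients in the two kinds of arm have had different amounts of contact. The contrast on quality of life (a primary outcome), perceived stress and HADS would then mix technique with number of contacts.

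A third, smaller consequence is that section 7 counts these patients towards low compliance, so adherence figures would treat a good outcome as poor adherence.

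**Working it through.** **Step 1. The plan's own figures.** Four sessions at two-week spacing: 4 × 2 = 8 weeks, which agrees with the stated course of about two months. The interview threshold: 0.75 × 4 = 3 sessions.

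**Step 2. The session rules side by side.**

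| Arm | Sessions planned | Stop at healing stated? |
|---|---|---|
| TG1, TG2 | 4 (section 4.1.1) | Not in 4.1.1; yes in section 7 |
| ACG | 4 (section 4.1.2) | Nowhere |
| PCG | 0 (section 4.1.2) | Not applicable |

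**Step 3. The stop against the threshold.** For a treatment-arm patient whose sessions end at healing:

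| Sessions received | Share of four | Can be invited? |
|---|---|---|
| 1 | 25% | No |
| 2 | 50% | No |
| 3 | 75% | Yes |
| 4 | 100% | Yes |

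This takes the denominator as the four planned sessions. Section 7 supports that reading: a stop at healing could not lower compliance if compliance were counted on sessions due up to healing.

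**Step 4. How many patients.** The article gives no healing rate, so this step is an illustration. Assumptions: a share p of the arm has healed by week 8, with p = 10%, 20% or 40%; the healing hazard is constant; 42 patients per arm (section 5.1); sessions at weeks 0, 2, 4 and 6, so that session 3 falls at week 4 and session 4 at week 6.

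- Weekly hazard h = −ln(1 − p)/8
- Healed before week t = 1 − exp(−h·t)

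| p | h per week | Before session 3 (t = 4) | Of 42 | Before session 4 (t = 6) | Of 42 | Mean sessions |
|---|---|---|---|---|---|---|
| 10% | 0.0132 | 5.1% | 2.2 | 7.6% | 3.2 | 3.85 |
| 20% | 0.0279 | 10.6% | 4.4 | 15.4% | 6.5 | 3.69 |
| 40% | 0.0639 | 22.5% | 9.5 | 31.8% | 13.4 | 3.34 |

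Mean sessions is the sum of exp(−h·s) over s = 0, 2, 4, 6.

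**Step 5. Sensitivity to the start.** If the first session is at week 2, session 3 falls at week 6. The ineligible share is then 7.6%, 15.4% or 31.8%, and mean sessions are 3.75, 3.49 or 2.94. Step 4 therefore uses the milder schedule.

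**Step 6. The ACG comparison.** If ACG sessions continue after healing, healing costs ACG no sessions, and the gap in mean sessions is 4 − 3.85 = 0.15 to 4 − 3.34 = 0.66 per patient under step 4. If ACG sessions also stop, all three arms follow the same rule and patients who heal on the same day have the same number of contacts.

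**The case against.** The strongest reply has five parts.

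- **A reader might infer that the stop applies to the treatment arms only.** The article does not say so. The sentence stands in a passage about compliance in the treatment groups, so naming them may only keep to that topic. The ACG description is silent on healing, and a session manual may settle it. This stands, so the attention mismatch is conditional on ACG sessions continuing.
- **A reader might infer that the healing comparison is biased.** It is not, by this route. Sessions lost after complete epithelization cannot change whether or when that ulcer first healed, and under the intention-to-treat approach of section 5.2 the stop can be part of the assigned strategy. This stands.
- **A reader might infer that T1 moves forward when sessions stop.** Section 3.1 puts it "at the end of the intervention/two months later at post-test (T1". With a planned course of about two months, both expressions name the same visit. Section 4.1.2 promises control patients the same intervals, and a footnote to Table 1 provides for ulcers already healed at T1. The documents do not support a shifting T1.
- **The interview harm is limited.** Patients who heal after session 3 stay eligible. Positive progression does not require complete healing, so improving but unhealed patients can fill those places. The analysis is thematic, with no effect estimate to bias. All this is fair. It limits the harm but leaves the earliest healers excluded because of their outcome.
- **Asking for substantial exposure before an interview about the sessions is defensible.** True, but the article does not say whether the threshold is meant to exclude patients who stopped because they healed.

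**Conclusion.** The session rules in sections 4.1.1, 4.1.2 and 7 conflict and must be reconciled. Two consequences hold, with different force.

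- **Interview eligibility: holds whatever ACG does.** Treatment-arm patients who heal before session 3 cannot be invited, so eligibility depends on the outcome that the sampling is meant to span. The size is about 5% to 23% of a treatment arm, resting wholly on the assumed 10% to 40% healed by week 8, the constant hazard and a first session at week 0. It is larger with a start at week 2.
- **Attention control: holds only on the literal reading,** in which ACG sessions continue after healing. It then concerns quality of life, perceived stress and HADS. No effect on those scales can be sized from the article. If ACG sessions also stop, the asymmetry disappears.

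The point does not extend to the healing endpoint, to the date of T1, or to fast healers in general. It is worth correcting because two stated rules work against each other and the correction is cheap. Which stopping rule is right is not for a statistical review to say.

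**What to change.** 1. Reconcile sections 4.1.1, 4.1.2 and 7 so that one rule on sessions after healing is stated and applies equally to TG1, TG2 and ACG. The choice of rule is the sponsor's.
2. In section 2.3, compute the 75% as sessions received divided by sessions due before the healing date, so that healing does not make a patient ineligible.
3. Report sessions not given because the ulcer had healed separately from non-compliance.

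The cost is a few sentences of wording and a healing date in the session record, which time to complete wound healing (section 3.5.4) already needs. The downside is small: some interviewees will have had only one or two sessions and can say less about the full course.
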